### Recruitment

Prior to recruitment, an audit will be carried out by the surgical and ethical team to evaluate the safety measurements at the research site in the Hasanuddin Dental Hospital. Patients will be recruited from an existing database of patients eligible for the proposed treatment available from the Hasanuddin University, Hasanuddin Dental Hospital.

### Randomization and treatment allocation

Because this is a first-in-human study, it is not possible to keep all personnel blinded to the assignment group. After written informed consent will be obtained by the main surgeon, randomization will be performed with regard to the treatment group. Central randomization using a randomization program on a secure computer will be used after the completion of patient enrollment. Patients will receive a unique study code, and their data will be provided to the clinical and research evaluators in a patient-coded manner.

### Blinding

The radiologist and the histopathologist will be kept blinded to the treatment when evaluating the data (Fig. 1).

**Fig. 1 Fig1:**
[figure not shown]
Protocol flowchart

### Data collection and access

The rules and responsibilities will be provided to the research team. The doctors and nurses of the research team will collect the data according to the evaluation (Table 1). All research team members will receive training on how to collect data at all study visits. The patient-coded data will be then handed over to the clinical evaluators and investigators. Each patient will be followed up for up to 6 months. The confidentiality of the participant’s data will be well protected by the data manager.

### Outcomes

#### Safety assessment based on physical examination and laboratory measurements

When a SAE occurs, it will be concluded that polyP is not (yet) safe in the current setting. For AEs, if they do not occur at a higher frequency than in patients treated with standard care (autologous bone) and/or can be resolved by non-invasive conventional methods (e.g., analgesics, antibiotics), the polyP product will be considered safe. In all other cases, polyP will not be considered safe (yet).

#### Radiographic evaluation

The Chelsea scale will be used to evaluate the bone graft and the level of the bone in comparison with the adjacent teeth. This scale starts with drawing an imaginary midline between the two teeth on either side of the cleft site. Each of those teeth (mesial and distal roots) will be divided starting from the cemento-enamel junction to the root apex in four parts. A 0 score is given when no bone is present up till the midline; a 0.5 score is given when there is bone, but it fails to reach the midline; and a 1 score is given when the bone extends from the root surface to the midline [23].

#### Histological and histomorphometric analysis

The histological and histomorphometric analysis will be performed in at least 3 patients from each group. In those patients, the dental implant site will be prepared using a trephine burr (⌀ 2.0 mm × 10.0 mm in length) instead of a normal drill, thereby being able to collect a biopsy from the treated site without interfering with the normal procedure. The biopsies will be fixed in 10% formalin and processed for embedding in methylmethacrylate for the evaluation of hard tissue formation. After sectioning, different stainings (Goldner’s trichrome, Toluidin blue, tartrate-resistant acid phosphatase (TRAP)) will be used, and histomorphometric parameters for bone formation will be analyzed. Two trained examiners, blinded for the treatment modality, will evaluate the images, and intra- and inter-observer reliabilities will be determined. In case of disagreement between the observers, the specimen will be re-evaluated to reach a consensus.

#### Monitoring

Monitoring will be done constantly by internal monitors of the Ethics and Research Committee of Faculty of Medicine, Hasanuddin University. Since there is a negligible risk, a data safety monitoring board will not be formed. A safety report will be provided to the Medical Research Ethics Committee of the Ethics and Research Committee of Faculty of Medicine, Hasanuddin University, every year. An interim analysis will not be conducted.

#### Statistical analysis

A SPSS power analysis for parameter comparisons between the groups will be performed. A *p* value less than 0.05 will be considered statistically significant.

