### Primary objective

The primary objective is to assess the safety of amorphous Ca-polyP MPs as a graft material in the human alveolar cleft reconstruction model.

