### Sample size

Since this is a first-in-man trial, the current trial sample size has been limited to only 2 × 4 patients, with the primary goal to gain a first insight on the safety and feasibility of the treatment with Ca-polyP. It is assumed that no SAEs or AEs will occur, and then, an n = 4 for each group should therefore be sufficient.

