For the clinical evaluation of bone formation, radiographic imaging will be applied. We are well aware that this will likely be relatively reliable in the case of the group that is treated only with the (radiolucent) polyP microparticles but will not be easy with the BCP/polyP treatment group. The BCP scaffold will be radiopaque and cause signal scattering, which will preclude accurate visualization of new bone formation within the scaffold material. We will circumvent this limitation by our histological and histomorphometrical analysis of the biopsies taken at the 6-month follow-up time point, during dental implant placement. This will enable us to still evaluate the bone formation at the microscopic level and to quantify multiple bone formation-related parameters and cellular activities as demonstrated before in other bone regeneration studies performed by our group [29, 30, 36, 37].

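### The statistical section names a power analysis as the between-group method, and its 0.05 rule does not fit 3 to 4 patients per arm

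*Protocol article*

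**What the plan says.** The Statistical analysis section has two sentences. The first reads "A SPSS power analysis for parameter comparisons between the groups will be performed". The second says that a p "value less than 0.05 will be considered statistically significant". No comparison test and no sidedness is given.

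Four other sections bear on it:

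- **Sample size:** "the current trial sample size has been limited to only 2 × 4 patients", because the trial is first-in-man. The reason given for its adequacy is "It is assumed that no SAEs or AEs will occur, and then, an n = 4 for each group should therefore be sufficient".
- **Histological and histomorphometric analysis:** this work "will be performed in at least 3 patients from each group". Table 1 lists a biopsy at day 180 without restricting it to a subset, so each arm may supply 3 or 4 specimens.
- **Discussion:** radiographs are expected to be hard to interpret in the arm that receives biphasic calcium phosphate (BCP). The authors write "We will circumvent this limitation by our histological and histomorphometrical analysis of the biopsies taken at the 6-month follow-up time point".
- **Primary objective:** "The primary objective is to assess the safety of amorphous Ca-polyP MPs as a graft material". Bone formation comes under the secondary objective.

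**The concern.** The only instruction for comparing the arms names a procedure that does not compare them. The sentence has two possible readings, and neither works:

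- **Prospective power calculation.** The sample size is already fixed on other grounds, and the article supplies none of the inputs such a calculation needs.
- **Power computed from the observed data.** For a given test and sample size this only re-expresses the p value and adds no information about the difference.

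The 0.05 rule is then left to act on whatever test is eventually used, with 3 or 4 patients per arm. Because the Discussion turns to histology where radiographs are unreliable, the bone-formation comparison leans on the outcome that may have the fewest patients. A result above 0.05 there would say little about whether the arms differ, yet the rule invites it to be reported as a finding.

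**Working it through.** **Inputs from the article.** Four patients per arm (Sample size); at least 3 per arm with histology, so 3 v 3, 3 v 4 or 4 v 4; threshold p strictly below 0.05.

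**Assumptions.** Sidedness is not stated: two-sided is assumed and one-sided is shown as a variant. No test is named: an exact rank test (Wilcoxon-Mann-Whitney) and a two-sample t test are both examined. No effect size is given: differences of 1, 2 and 3 SD are illustrative.

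**The plan's own figure.** The 4 per group cannot be reproduced. The article states no effect size, SD, power or event rate, so no sample-size formula applies.

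**Step 1: smallest attainable exact rank p.** The most extreme result is complete separation of the arms, without ties. Its p value is 1/C(n1+n2, n1) one-sided and twice that two-sided.

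| Specimens | C(n1+n2, n1) | Minimum two-sided p | Minimum one-sided p |
|---|---|---|---|
| 3 v 3 | 20 | 2/20 = 0.100 | 1/20 = 0.050 |
| 3 v 4 | 35 | 2/35 = 0.057 | 1/35 = 0.029 |
| 4 v 4 | 70 | 2/70 = 0.029 | 1/70 = 0.014 |

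Two-sided, the threshold is out of reach at 3 v 3 and 3 v 4. At 4 v 4 the next most extreme ordering has p = 4/70 = 0.057, so only complete separation passes. One-sided, 3 v 3 still fails the strict inequality, while 3 v 4 and 4 v 4 can pass.

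**Step 2: dependence on how the p value is computed.** For the same completely separated data, the two-sided normal approximation gives:

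| Specimens | No continuity correction | With continuity correction |
|---|---|---|
| 3 v 3 | 0.0495 | 0.081 |
| 3 v 4 | 0.034 | 0.052 |
| 4 v 4 | 0.021 | 0.030 |

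At 3 v 3, identical data are therefore significant by one computation (0.0495) and not by another (0.100).

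**Step 3: power of a two-sided t test.** Power comes from the noncentral t distribution with n1+n2−2 degrees of freedom and noncentrality d/√(1/n1+1/n2), where d is the difference in SD units. At d = 1 the noncentrality is 1/√(2/3) = 1.22 for 3 v 3 and 1/√(1/2) = 1.41 for 4 v 4.

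| Specimens | Power, d = 1 | Power, d = 2 | Power, d = 3 | d for 80% power |
|---|---|---|---|---|
| 3 v 3 | 16% | 46% | 78% | 3.07 |
| 3 v 4 | 19% | 56% | 88% | 2.68 |
| 4 v 4 | 22% | 66% | 94% | 2.38 |

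For comparison, the exact two-sided rank test at 4 v 4, simulated under normal data, has power of 14%, 49% and 83% at d = 1, 2 and 3.

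**Step 4: intervals have the same limit.** A distribution-free interval for the between-arm difference, obtained by inverting the exact rank test, covers at most 1 − 2/20 = 90% at 3 v 3, 1 − 2/35 = 94.3% at 3 v 4 and 1 − 2/70 = 97.1% at 4 v 4. With 3 specimens in either arm, a 95% interval needs a distributional assumption that 3 or 4 values cannot check.

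**The case against.** The strongest reply is that this is a pilot that claims no power, that the between-arm contrast is not its main question, and that the choice of test can be left to an analysis plan that is not shown. Much of that stands, and it limits what can be inferred.

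- **That no histology result could be significant.** A reader might infer this from the rank-test floor. The documents do not support it. Three specimens per arm is a minimum, at 4 v 4 the exact two-sided test can reach 0.029, and the article names neither a rank test, nor an exact p, nor sidedness. A t test has no floor.
- **That safety will be reported as no significant difference.** A reader might apply Fisher's exact test to adverse events and note that only 4/4 v 0/4 falls below 0.05 (0.029; 3/4 v 0/4 gives 0.143). The article announces no such test. The Outcomes section judges safety by whether a serious adverse event occurs and, for other events, by their frequency relative to standard care and/or whether they resolve with non-invasive conventional methods. No between-arm p value enters.
- **That the trial claims equivalence of its arms.** It does not. Misreading a non-significant result is a risk to guard against, not a statement in the protocol.

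The reply does not rescue the first sentence of the section. Leaving the test to an analysis plan is ordinary; naming a power analysis in its place is a wrong statement, not an omission. Nor does pilot status justify the 0.05 rule: a trial that seeks first insight has no need of it.

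**Conclusion.** The point holds in a limited form. The stated method for between-group comparison is wrong as written, whichever test is later chosen. The 0.05 rule is poorly matched to the design: unreachable by an exact two-sided rank test if either arm has only 3 specimens, reachable at 4 v 4 only under complete separation, and by t test dependent on differences of roughly 2.4 to 3.1 SD for 80% power. At an assumed difference of 1 SD, t-test power is 22% (4 v 4) or 16% (3 v 3).

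The rank-test figures rest on an exact, two-sided test without ties. The t-test figures rest on normality and equal variances. The consequence is confined to the secondary bone-formation comparison; the primary safety conclusion is unaffected.

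**What to change.** Replace the Statistical analysis section with a descriptive plan, deleting both the power-analysis sentence and the 0.05 decision rule. It should state that:

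- adverse events, serious adverse events and feasibility failures are reported as counts with exact 95% confidence intervals, per arm and pooled over the 8 patients exposed to polyphosphate;
- radiographic and histomorphometric values are listed and plotted for each patient, with median and range per arm;
- any between-arm difference or test is exploratory, with its method named and the attainable coverage of its interval stated (for an exact rank-based interval, at most 90% at 3 v 3 and 94.3% at 3 v 4);
- a non-significant result is not read as similarity of the arms.

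The cost is one paragraph of wording, with no extra patients, visits or measurements. The trial gives up a formal claim of significance between arms.

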#### Amendments

All substantial amendments will be notified to the ethical committee and competent authority to ensure the safety and integrity of participants as well as the scientific value of the trial.

#### Post-trial care

All participants will be kept in secondary follow-up for a period of 3 years to ensure their safety and to record any delayed side effects of the Ca-polyP graft material.

## Discussion

This is the first-in-man study evaluating the potential regenerative capacity of polyP using an alveolar cleft model. PolyP represents a completely novel type of regenerative compound, since it can be considered as a rich energy source for tissue repair, which may be as pivotal for the bone regeneration process as the osteogenic factors, which are generally believed to be the primary active compounds [14]. The high-energy phosphate bonds of polyP are identical to those present in the “common” cellular energy molecule ATP, and both serve as substrates for the enzyme alkaline phosphatase (ALP), a well-known marker for active bone formation [12]. PolyP has also been reported to promote mineralization [24] and to increase progenitor cell differentiation into osteoblasts [15, 25]. PolyP is present in platelets, which play an essential role in early wound repair. Interestingly, platelet-rich plasma (PRP), a concentrate of platelet-rich plasma protein derived from the whole blood and often used in bone repair strategies, therefore will also contain polyP. However, the efficacy of PRP to promote bone repair is nowadays questioned, since both positive and neutral/negative effects have been published recently [26, 27]. We speculate that the much higher dose of polyP present in our preparations will be well above the bone regeneration threshold, and thus may have a positive effect on the bone repair process.

Calcium phosphate ceramics including biphasic calcium phosphates (BCPs) have been widely used as bone substitutes and tissue engineering scaffolds. Calcium phosphates are highly biocompatible, proven to be safe, and successfully used in many different clinical treatment modalities such as bone augmentation in spinal arthrodesis, maxillo- and craniofacial surgeries, orthopedics, periodontal treatment, and metallic implant coatings [28–33]. Some reports describe that BCP may also have osteoinductive properties [34], which implies that BCP may add to the osteoinductivity as well. Moreover, a recent clinical study applying microstructured β-TCP for alveolar cleft repair demonstrated that calcium phosphate could be used safely and effectively for this purpose as well [35]. We are therefore convinced that the Straumann Bone Ceramic used in the current study will be a safe-to-use scaffold and may have a supportive or even synergistic effect on the bone formation when combined with the bioactive polyP.

For the clinical evaluation of bone formation, radiographic imaging will be applied. We are well aware that this will likely be relatively reliable in the case of the group that is treated only with the (radiolucent) polyP microparticles but will not be easy with the BCP/polyP treatment group. The BCP scaffold will be radiopaque and cause signal scattering, which will preclude accurate visualization of new bone formation within the scaffold material. We will circumvent this limitation by our histological and histomorphometrical analysis of the biopsies taken at the 6-month follow-up time point, during dental implant placement. This will enable us to still evaluate the bone formation at the microscopic level and to quantify multiple bone formation-related parameters and cellular activities as demonstrated before in other bone regeneration studies performed by our group [29, 30, 36, 37].

## Conclusion

With this protocol, we summarized how we intend to evaluate the safety and feasibility of Ca-polyP MP as a new grafting material in an alveolar cleft model.

## Trial status

Recruitment started in November 2019 and is planned to end in September 2020, with 8 patients randomized. The current protocol version is 1.0, dated 28 May 2019.
